**5.5. Group Allocation Method**

5.5.1. Randomization Method

Randomization codes in a 1:1 ratio for the treatment and placebo groups will be generated using the SAS statistical software package by a statistician who is not involved in data management or analysis. A block randomization design will be used, with each block including one subject in the exosome treatment group and one in the placebo group.

Drug assignment codes will be created by a statistician unaffiliated with the study. The randomization system will be available 24 hours a day. Investigational drugs will be administered according to the order of enrollment using corresponding random numbers.

The randomization codes (sealed blind codes) will be prepared in duplicate and securely stored by the principal investigator and the clinical trial pharmacy at the study institution.

Randomization and blinding will be guided by the Biostatistics Department of Hainan Medical University.

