# 6. Sample Size Requirement

This study is a randomized, placebo-controlled, exploratory clinical trial. A total of 24 subjects will be enrolled at the First Affiliated Hospital of Hainan Medical University, with 12 subjects assigned to the treatment group and 12 to the placebo group.

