**11.3. General and Baseline Characteristics**

(1) Demographic information, prior medication history, and comorbidities will be descriptively summarized.

(2) For quantitative variables like age, baseline comparisons between groups will be performed using grouped t-tests or Wilcoxon rank-sum tests, depending on the characteristics of the variables. For categorical variables like gender or comorbidities, comparisons will be made using chi-square or Fisher's exact tests.

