**11.4. Efficacy Evaluation**

(1) Primary Efficacy Evaluation:

The proportion of patients who experienced disease progression events within 84 days after enrollment or by the end of follow-up will be calculated and compared between groups using the chi-square test.

(2) Secondary Efficacy Evaluation:

Proportions of individual disease progression events will be compared using chi-square or Fisher's exact tests. Time to disease recovery and symptom improvement will be analyzed using grouped t-tests or Wilcoxon rank-sum tests.

(3) Other Observational Indicators:

Changes in IL-6 levels post treatment will be compared between groups using repeated measures analysis. Comparisons at different time points will be made using t-tests. Quality of life scores and total hospitalization costs will also be compared using t-tests or Wilcoxon rank-sum tests.

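### Time to recovery and time to improvement are assigned to t-test or rank-sum with no rule for patients who never recover; a minor companion point is the unspecified chi-square for the primary proportion at 12 per arm

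*Protocol*

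**What the plan says.** Protocol Section 11.4(2), on secondary efficacy: "Time to disease recovery and symptom improvement will be analyzed using grouped t-tests or Wilcoxon rank-sum tests". No rule says how a patient without recovery or improvement enters that comparison.

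Three other places bear on it:
- Section 11.2 puts primary and secondary efficacy on the intention-to-treat principle.
- Section 5.3 carries the last major efficacy assessment of a withdrawn patient forward as the final result. That gives a final status, not an event time.
- Section 6 fixes the size, "with 12 subjects assigned to the treatment group and 12 to the placebo group", with no effect size, event rate or power behind it.

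For the primary efficacy analysis, Section 11.4(1) takes "The proportion of patients who experienced disease progression events within 84 days after enrollment or by the end of follow-up", which "will be calculated and compared between groups using the chi-square test". For secondary proportions the text is wider: "Proportions of individual disease progression events will be compared using chi-square or Fisher's exact tests". Section 11.3 gives the same choice for baseline categories: "comparisons will be made using chi-square or Fisher's exact tests".

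**The concern.** The protocol itself expects patients without an event. It enrols idiopathic pulmonary fibrosis and COPD with fibrosis (Section 5.1), names poor efficacy as a reason to withdraw (Section 5.3), provides for loss to follow-up (Section 8.1) and lists lack of efficacy among the possible events (Section 10.6). Their times are censored. A t-test has no place for a censored time, and a rank-sum test has one only if a rule places these patients in the ranking.

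Two routes remain open:
- Analysing recoverers only compares groups selected after randomization. It asks whether those who recovered did so faster and ignores whether more of them recovered.
- Assigning a value to the others keeps everyone, but the protocol does not define that value.

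At stake is whether the same data can give very different answers depending on a choice that the text leaves open. The chi-square wording raises a smaller version of the same problem for the primary proportion.

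**Working it through.** The plan states no figure that can be reproduced here. Its only number is 12 per arm.

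**Time endpoints**

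From the protocol: 12 per arm, last scheduled efficacy visit D84, two-sided 5% level. Assumed: exponential event times, complete follow-up to day 84, and 29% placebo recovery by day 84.

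- Placebo hazard: −ln(1 − 0.29)/84 = 0.3425/84 = 0.00408 per day.
- Recovery by day 84 at hazard ratio h is 1 − 0.71^h. This gives 50%, 64% and 75% at h = 2, 3 and 4.
- Chance of at most one recoverer among 12 placebo patients, when the recoverers-only t-test cannot sensibly be run: 0.71^12 + 12 × 0.29 × 0.71^11 = 0.016 + 0.080 ≈ 10%.

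Rejection rates from repeated simulation (about 4,000 trials or more per scenario; ranges show the spread between runs):

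| Analysis | HR 2 | HR 3 | HR 4 |
| --- | --- | --- | --- |
| t-test, recoverers only | 5–7% | 6–7% | 7–8% |
| t-test, non-recoverers set to day 84 | 15–16% | 36% | 57–59% |
| Rank-sum, non-recoverers tied at day 84 | 16–17% | 39–40% | 60–62% |
| Log-rank, non-recoverers censored at day 84 | 18–19% | 42–43% | 64–67% |

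At hazard ratio 2 the recoverers-only mean difference points the wrong way in about 45% of trials. With no effect, the three analyses that keep everyone reject in about 4% to 6%.

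Other assumed recovery rates (3,000 trials each) give the same picture:

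| Recovery by day 84 | Recoverers-only t-test | Recoverers-only rank-sum | Worst-rank rank-sum | Log-rank |
| --- | --- | --- | --- | --- |
| 75% v 25% | 0.09 | 0.07 | 0.70 | 0.74 |
| 80% v 40% | 0.09 | 0.07 | 0.52 | 0.58 |
| 50% v 20% | 0.06 | 0.03 | 0.31 | 0.33 |

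The recoverers-only columns count only trials with at least two recoverers per arm.

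**Primary proportion**

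With m progressions among 24 patients, the expected counts per arm are m/2 and (24 − m)/2. Both reach 5 only if m is 10 to 14. At least one falls below 5 with probability 98.7% at a 20% event rate, 84.8% at 30% and 51% at 40%.

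True size by full enumeration of the 13 × 13 outcomes:

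| Event rate | 5% | 10% | 20% | 30% | 40% | 50% |
| --- | --- | --- | --- | --- | --- | --- |
| Uncorrected Pearson | 0.2% | 1.5% | 3.9% | 4.9% | 5.9% | 6.4% |
| Fisher (Yates the same) | 0.02% | 0.3% | 1.2% | 1.7% | 2.1% | 2.3% |

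Apart from swapping arms, eight outcome patterns are significant by uncorrected Pearson but not by Fisher. For 0/12 v 4/12:
- Pearson: 24 × (0 × 8 − 12 × 4)² / (12 × 12 × 4 × 20) = 55,296/11,520 = 4.8, p = 0.028.
- Yates: 24 × (48 − 12)² / 11,520 = 2.7, p = 0.100.
- Fisher: 2 × 495/10,626 = 0.093.

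Another pattern is 1/12 v 6/12: 0.025 by Pearson and 0.069 by Fisher. With Yates correction, chi-square and Fisher agree on significance in every 12 v 12 table.

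**The case against.** A reader might infer that the plan discards patients who never recover and that its time comparison therefore has almost no power. The documents do not support this. No sentence drops anyone, and Section 11.2 argues against it. The near-zero power belongs to the recoverers-only reading alone. A rank-sum test with non-recoverers tied at the worst rank needs no invented time and, with complete follow-up, loses only a few points against log-rank. The handling rule could also sit in a statistical analysis plan that is not at hand.

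That much stands. It does not remove the defect: the protocol fixes the tests, one of them (the t-test) has no worst-rank version, and complete follow-up is not assured when Sections 5.3 and 8.1 provide for withdrawal and loss.

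The simulation also idealises the data. Table 1 schedules the symptom scales after baseline only at D8, D28 and D84 (Section 2.2 adds Day 4), so real times would be coarse and heavily tied. Recovery is undefined, and time to recovery appears in neither Section 2.2 nor Section 9.1. These objections stand too, and they limit how literally the power figures can be read.

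On chi-square, a reader might infer a serious false-positive problem. There is none: uncorrected Pearson is at or below 5% up to a 30% event rate and exceeds it by at most 1.4 points. Fisher is the more distorted of the two, on the conservative side, and costs power (0.43 against 0.60 at assumed rates of 50% v 10%). Pearson against Fisher is partly preference.

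**Conclusion.** The point holds as a gap in a method that the protocol does fix. Section 11.4(2) names tests that cannot take censored times and gives no rule for patients without an event. Under the assumed rates, what the analyst then does moves the rejection rate at hazard ratio 3 from about 6% (recoverers only) to about 40% (everyone kept, rank-sum) or 43% (log-rank). These figures rest on assumed recovery rates, exponential continuous times and complete follow-up. The ordering held for every set of rates tried.

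The chi-square point is minor. The primary proportion alone lacks the exact option offered for secondary and baseline proportions, and the unstated version of the test can decide significance at p ≤ 0.05 in eight outcome patterns.

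The consequence of both is limited: this is an exploratory phase I trial with a safety primary objective and no power claim. The wording should still be corrected before analysis.

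**What to change.** In Section 11.4(2), replace the t-test and rank-sum sentence with Kaplan-Meier curves and a log-rank test on all randomized patients. Censor those without the event at their last assessment. Count death as never recovering, by keeping those patients at risk to the end of follow-up. If follow-up is complete, a rank-sum test with non-recoverers tied at the worst rank is an acceptable alternative, provided the rule is written down. State what counts as recovery and as improvement, and that event times are known only to the visit.

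In Section 11.4(1), name one test in advance, preferably an unconditional exact test with an exact confidence interval for the difference in proportions. Fisher's test alone is defensible but conservative at this size.

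The cost is a few lines of wording and no new data collection. Exact p-values will be somewhat larger than uncorrected chi-square ones, and the coarse visit schedule will still limit what any time analysis can show.

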**2.1. Primary Objective**

To evaluate the safety of inhaled extracellular vesicle therapy in patients with pulmonary fibrotic lesions as identified by high-resolution computed tomography (HRCT).

1. to monitor vital signs, clinical symptoms and signs, and the incidence of adverse events on Days 1–8, Week 4, and Week 12 after enrollment.
2. to assess changes in laboratory and clinical parameters on Day 8 and Week 12, including complete blood count, urinalysis (plus pregnancy test), blood biochemistry, electrocardiogram (ECG), peripheral oxygen saturation (SpO₂), tumor markers, levels of IL-6 and IL-10, immune cell function in peripheral blood, and lymphocyte subsets.

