# 9. Efficacy Evaluation Criteria

**9.1. Efficacy Assessment**

(1) Primary Efficacy Endpoints

- Clinical symptoms and signs
- Pulmonary function
- High-resolution chest CT (HRCT)
- Frequency and severity of acute exacerbation events

(2) Secondary Endpoints

- 6-minute walk distance (6MWD), including grade and distance
- St. George's Respiratory Questionnaire (SGRQ)
- Leicester Cough Questionnaire
- Modified Medical Research Council Dyspnea Scale (mMRC)

(3) Other Observational Indicators

- Post-treatment changes in IL-6 levels, peripheral blood immune cell function, and peripheral blood lymphocyte subsets.

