**11.2. General Principles**

The efficacy report of this study, including both primary and secondary efficacy endpoints, will be based on the Intention-To-Treat (ITT) principle. The analysis strategies are as follows:

1. Quantitative variables will be described using mean (standard deviation), median (minimum, maximum, or interquartile range). Categorical variables will be presented as counts (percentages).
2. All statistical tests will be two-sided. A p-value ≤ 0.05 will be considered statistically significant.
3. Enrollment and Completion Status

The number of enrolled and completed cases will be summarized, and a list of dropout cases will be provided. The total dropout rates between groups will be compared using the chi-square test.

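### Minor: the per-visit IL-6 t-tests in section 11.4(3) would be better replaced by Day 8 and Day 84 contrasts from the planned repeated-measures analysis, fitted to log IL-6 with baseline adjustment

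*Protocol*

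**What the plan says.** Section 11.4(3) of the protocol gives IL-6 two analyses. The first is "Changes in IL-6 levels post treatment will be compared between groups using repeated measures analysis". The second, in the next sentence, is "Comparisons at different time points will be made using t-tests". The sentence after that covers other variables and does offer a rank test: "Quality of life scores and total hospitalization costs will also be compared using t-tests or Wilcoxon rank-sum tests".

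Neither IL-6 sentence states a scale or a baseline covariate. The second does not say whether the t-tests use post-treatment values or changes. Table 1 schedules IL-6 on D0, D8 and D84, so there is one baseline and two later values.

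The sample size section gives 24 patients, "with 12 subjects assigned to the treatment group and 12 to the placebo group". Section 11.2 sets the test: "All statistical tests will be two-sided" and "A p-value ≤ 0.05 will be considered statistically significant".

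Section 9.1 lists IL-6 in its third tier, below the primary and secondary endpoints: "Post-treatment changes in IL-6 levels, peripheral blood immune cell function, and peripheral blood lymphocyte subsets". IL-6 also appears among the laboratory parameters of the primary safety objective in section 2.1 ("levels of IL-6 and IL-10, immune cell function in peripheral blood").

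**The concern.** The t-test is a stated choice for the per-visit IL-6 comparisons. The protocol offers a rank alternative for quality of life, for costs and, in section 11.3, for baseline variables, but not for IL-6.

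IL-6 is a positive concentration. If its distribution is right-skewed, one or two high values can dominate the mean and SD in groups of 12. A t-test on post-treatment values also leaves the D0 measurement unused. A t-test on changes uses D0 with a fixed weight of one, which is inefficient unless the correlation with baseline is high. With 24 patients, precision has to come from the analysis.

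The plan also yields two sets of IL-6 results, one from the repeated-measures analysis and one from the t-tests. They may differ, and nothing says which is to be read. At stake is how clearly an exploratory marker can be interpreted, not a conclusion of the trial.

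**Working it through.** **Inputs from the protocol.** 12 per arm; two-sided 0.05; IL-6 on D0, D8 and D84. The protocol gives no SD, correlation, target effect or power for IL-6, so there is no planned figure to reproduce.

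**Assumptions.** Log-normal IL-6 with log-SD 0.5 to 1.0; baseline correlation ρ from 0.3 to 0.8 on the log scale, with ρ = 0 looked at separately; EV halves IL-6 unless stated; complete data.

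**Step 1: baseline adjustment alone, same scale.** Relative to a t-test on post values, the variance factor is 2(1 − ρ) for a change-score t-test and (1 − ρ²)(1 + 1/(2n − 4)) for ANCOVA, with n = 12. Power for a true effect of 1 SD (noncentral t, 22 df; 21 df for ANCOVA):

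| ρ | post-value t | change t | ANCOVA |
|---|---|---|---|
| 0.3 | 65% | 51% | 67% |
| 0.5 | 65% | 65% | 75% |
| 0.7 | 65% | 86% | 89% |

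At ρ = 0, ANCOVA loses about 2 points (63% against 65%).

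**Step 2: scale and baseline together, worked example.** Take log-SD 0.8 and ρ = 0.6. The standardised effect on the log scale is ln 2 / 0.8 = 0.693/0.8 = 0.866.
- t-test on log post values: noncentrality 0.866 × √(12/2) = 2.12, 22 df, power about 53%.
- ANCOVA on log values: factor (1 − 0.36)(1 + 1/20) = 0.672; noncentrality 2.12/√0.672 = 2.59, 21 df, power about 69%.
- t-test on raw post values, by simulation: about 41%.

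So the log scale adds about 12 points (41 to 53) and the baseline term about 16 (53 to 69).

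**Step 3: range.** Simulated power, 40,000 trials per row:

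| log-SD | ρ | raw post-value t | raw change t | log ANCOVA |
|---|---|---|---|---|
| 0.5 | 0.3 | 86% | 55% | 91% |
| 0.5 | 0.6 | 86% | 74% | 98% |
| 0.8 | 0.3 | 41% | 22% | 55% |
| 0.8 | 0.6 | 41% | 33% | 69% |
| 0.8 | 0.8 | 41% | 52% | 91% |
| 1.0 | 0.6 | 24% | 19% | 51% |
| 1.0 | 0.8 | 25% | 32% | 75% |

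The gain over the raw post-value t-test runs from 91 − 86 = 5 points to 91 − 41 = 50 and 75 − 25 = 50 points. If IL-6 doubles instead (log-SD 0.8, ρ = 0.6), the three figures are about 41%, 52% and 69%.

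**Step 4: type I error.** With no effect, log ANCOVA rejected in about 5% of trials and the raw t-tests in 3.4% to 4.9%. The higher power is not bought with excess false positives.

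**Limits.** The repeated-measures analysis itself was not simulated, because its terms are not given. The figures describe the per-visit comparisons only. ANCOVA at one visit stands in for the visit contrast of the proposed model.

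**The case against.** The strongest objection is that the repeated-measures comparison comes first and concerns changes, so the D0 value may well enter there. The t-tests are an additional per-visit step. A reader might infer from the t-test sentence that the plan ignores baseline IL-6 altogether. The documents do not support that, and the point is confined to the per-visit comparisons.

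Second, the raw scale is inferred from silence. Scale and covariates are commonly left to the SAP, which section 11.1 mentions and which is not shown. This stands in part: the SAP could specify logs or changes. The protocol does name the t-test, however, and step 1 shows that even on a common scale neither form of it beats ANCOVA over ρ 0.3 to 0.7.

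Third, the size depends on inputs that the protocol does not supply. This stands. With low skewness and low correlation, the gain over a post-value t-test is small.

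Fourth, because IL-6 is part of the primary safety objective, a reader might infer that a safety-relevant rise would be missed. The documents do not support that either. The t-tests sit under efficacy in 11.4(3). Safety laboratory data are handled in section 11.5 by normal/abnormal change, descriptive summaries and flagging of abnormal values, none of which depends on a t-test.

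**Conclusion.** The point holds as a minor improvement. The per-visit t-tests are a stated method, and a better one exists on data already scheduled. In every scenario with a true effect that was examined, ANCOVA on log IL-6 had more power than either raw-scale t-test, with type I error near 5%. In the example (halving, log-SD 0.8, ρ = 0.6) power is 69% against 41% or 33%; over the range shown, the gain over the post-value t-test is about 5 to 50 points.

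The direction rests on right-skewed, roughly log-normal IL-6 and some correlation with baseline. The size rests on the assumed log-SD, correlation and effect. IL-6 is a third-tier indicator in an exploratory trial of 24 patients, and no decision rule in the protocol uses it.

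**What to change.** In section 11.4(3), delete the sentence on time-point t-tests. State instead that the planned repeated-measures analysis is fitted to log IL-6 at D8 and D84, with arm, visit, arm-by-visit and log baseline IL-6, and that the D8 and D84 comparisons are the arm contrasts from that model. Report the EV/placebo ratio of geometric means at each visit with a 95% confidence interval.

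The cost is wording only: no new samples, visits or patients. Results are then read as ratios rather than differences in concentration. If the assay can return values below its quantification limit, the SAP should say how these enter the log. If baseline correlation proves close to zero, the covariate costs about 2 points of power (step 1).

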**11.5. Safety Analysis**

A detailed listing of all adverse events occurring during the trial will be provided. Changes in laboratory results (normal/abnormal) before and after the trial and their relationship to the study drug will be assessed. The incidence of adverse events in each group will be summarized. Safety analyses will be based on the Safety Analysis Set and conducted by treatment group. Treatment-emergent adverse events (TEAEs) and serious adverse events (SAEs) will be summarized. Descriptive statistics will be used to summarize laboratory findings, symptoms, vital signs, physical examinations, and ultrasound results. Abnormal values will be flagged.

# 12. Follow-up Plan and Implementation

All case follow-up personnel in this trial received standardized training and guidance prior to the start of the study.

**12.1. Treatment Observation Period and Follow-up Methods**

Safety and efficacy observations will be conducted according to the study schedule. Additional safety follow-ups will be conducted via telephone visits at 6 and 12 months.

**12.2. Follow-up Content**

Follow-up assessments will be conducted according to the items marked in the clinical study flowchart. Detailed test items and methods are described in Section 4 – Study Design of the clinical trial protocol.

**12.3. Withdrawal from Study During Follow-up**

Subjects or their legal representatives have the right to withdraw from the study at any time and for any reason. Investigators also have the right to terminate a subject’s participation in the study. If a subject withdraws, the reason must be recorded in the Case Report Form (CRF).
